### Statistical analysis

Analysis of the data will be conducted according to the intention to treat principle [43]. The result of randomization will be checked by comparing baseline socio-demographic and clinical parameters between VRAPT and the waiting list condition, using univariate analyses (chi-square tests for dichotomous measures and t-tests for continuous measures). Differences in scores between pre-intervention, post-intervention and follow-up assessments and between intervention and control group will be examined for the dependent variables, using multilevel (repeated-measures) random linear regression analysis. Primary outcome measure is peak and general score as measured with the SDAS and self-report aggression measurement of participants. The SDAS and self-report measurement will be compared between VRAPT and waiting list, before, during and after VRAPT or waiting list. Effects of VRAPT will be tested with group x time interaction terms. Risk factors for aggression will be used as covariates in the linear regression models. Significance of fixed effects are assessed by Likelihood Ratio tests. Statistical significance of the regression effects will be tested using T-tests. In all analyses, a *p*-value < .05 will be considered statistically significant.

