### Research aims

The main objective of this study is to investigate the effectiveness of VRAPT in the reduction of reactive aggression in forensic psychiatric inpatients in four Dutch forensic psychiatric centers (FPCs). The primary outcome measure is the level of aggressive behavior, measured by staff-report and a self-report questionnaire. It is expected that both staff-observed and self-reported aggressive behavior will decrease after completion of VRAPT compared to being on the waiting list, and that differences will be maintained after a 12-week follow-up period. Secondary outcome measures are participant’s self-reported rates of anger, impulsivity, hostility, physiological arousal, and coping. As all these different components are contributing to the way a patient reacts to provocation of others.

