### Power and sample size calculation

There is no previous research using VR aggression regulation training in patient forensic populations based on which an effect size could be estimated. Conventional aggression regulation therapy in such settings has an effect size of around 0.3 [18]. An effect size of 0.5 is considered as moderate. Using this effect size with a β-power of .80, alpha of .05 and an independent two-sided t-test to evaluate the main outcome, 64 subjects are required in each condition, total *N* = 128.

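### Three primary scores are each tested at .05 with no stated success rule, while the sample size is justified for a single t-test of one main outcome

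*Protocol article*

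**What the plan says.** - **Primary outcome (Statistical analysis).** "Primary outcome measure is peak and general score as measured with the SDAS and self-report aggression measurement of participants". The SDAS subsection confirms that peak and general are separate scores, since each item is rated twice. The self-report measure listed under Primary outcome is the AVL. This gives three primary scores.
- **Test and threshold (Statistical analysis).** Effects are tested through group x time terms in a multilevel repeated-measures model. Likelihood ratio tests are used for fixed effects and t-tests for regression effects. In all analyses a p-value "< .05 will be considered statistically significant".
- **Sample size (Power and sample size calculation).** "An effect size of 0.5 is considered as moderate", and this value is used with power .80, alpha .05 and "an independent two-sided t-test to evaluate the main outcome, 64 subjects are required in each condition". The total is 128.
- **Expectation (Research aims).** "It is expected that both staff-observed and self-reported aggressive behavior will decrease after completion of VRAPT compared to being on the waiting list", with the differences maintained at 12 weeks. The Discussion repeats the hypothesis for both sources.

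The article does not say whether one, two or all three scores must be significant. It gives no order of testing and no division of alpha.

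**The concern.** Alpha and power describe a decision, and here the decision is left open. The sample size section assumes one main outcome and one test. The analysis section supplies three primary scores, each judged at .05. Depending on how the results are later read, one significant score could be presented as showing that VRAPT works, or failure on one score could be presented as failure of the trial. The first reading raises the false-positive rate above the stated .05. The second lowers the power below the stated .80 on the basis used to size the trial.

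This is more than a detail left to a fuller plan. The article itself fixes the three scores, the uniform threshold and the single-test sample size, and these do not fit together. The Discussion envisages implementation in other forensic centers if VRAPT proves effective, so what counts as proof matters.

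**Working it through.** **Inputs from the article:** d = 0.5, two-sided alpha .05, power .80, 64 per condition, three primary scores. **Assumed, because the article gives no values:** the same d for every score; peak-general correlation 0.5 to 0.9; SDAS-AVL correlation 0 to 0.5.

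**1. The stated figure, one test.** Noncentral t with 126 degrees of freedom and noncentrality 0.5 × √(64/2) = 2.83. Power is 0.801 at 64 per condition and 0.795 at 63. The stated 64 is reproduced.

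**2. Any one of three scores suffices, each at .05.**
- Independent scores: 1 − 0.95³ = 0.143.
- Correlated scores (multivariate normal simulation): 0.136 at correlations 0.5 (peak-general) and 0 (SDAS-AVL); 0.121 at 0.8 and 0.3; 0.108 at 0.9 and 0.5.
- The type I error is therefore about 11 to 14%. It would be higher if post-intervention and follow-up were also tested separately.

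**3. One SDAS score and the AVL must both succeed, each at .05.** Alpha is held. Joint power:
- Independent: 0.801² = 0.64.
- Correlation 0.3: 0.67.
- Correlation 0.5: 0.69.

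**4. All three must succeed, each at .05.** Alpha is held. Joint power:
- Independent: 0.8015³ = 0.51.
- Correlations 0.5 and 0: 0.55.
- Correlations 0.9 and 0.5: 0.66.

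**5. Alpha shared over three scores.** The first Holm step uses .05/3 = .0167. Power for a given score at 64 per condition is 0.656, and 86 per condition would be needed for .80. This is power per score. The chance that at least one score passes is higher: 1 − (1 − 0.656)³ = 0.96 if independent, falling towards 0.656 as the correlations approach 1.

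**6. Allowing for the planned model.** Let ρ be the pre-post correlation, which the article does not give.
- Baseline adjustment gives an effective d of 0.5/√(1 − ρ²). At ρ = 0.5 this is 0.577. Power is then 0.80 at .0167 and 0.90 at .05, so joint power for two independent scores is 0.90² = 0.81.
- A change-from-baseline contrast gives 0.5/√(2(1 − ρ)). At ρ = 0.5 this is 0.5, so there is no gain and power at .0167 stays at 0.656. At ρ = 0.7 it is 0.89.

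**The case against.** **The expectation names both sources.** Research aims and the Discussion both speak of staff-reported and self-reported aggression, and the Primary outcome subsection treats the two perspectives as complementary. On that reading no alpha adjustment between sources is needed. This stands in part, and it is why one cannot say, as a reader might infer, that the trial's conclusion has no controlled error rate. But the text states an expectation, not a decision rule, and does not say how the two SDAS scores count. Adopting it as the rule protects alpha but leaves the .80 unsupported on the stated t-test basis.

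**The number of tests.** A reader might count three scores at two times and arrive at six primary contrasts. The article does not fix that number. One likelihood ratio test of group x time per score covers all times and gives three tests. In Table 1 the SDAS is collected over observation periods, not at the AVL's assessment points. The section also provides for t-tests of regression effects, so separate tests by time are possible but not stated. The point stands on three tests alone.

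**The model may recover the power.** This also stands. The power figures in steps 3 to 5 are for an unadjusted t-test, and step 6 shows that a moderate pre-post correlation with baseline adjustment could restore about .80. A reader might infer that alpha .05 and power .80 cannot both hold at 128 participants. The article does not support so flat a claim, just as it gives no correlation that would support the opposite. A more efficient model would not in any case lower the type I error of an any-score rule.

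**Multiplicity can be left to the analysis plan.** The details can. The mismatch between the statements already made in the article remains.

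**Conclusion.** The point holds in this form: the stated alpha and power describe one test of one main outcome, whereas the plan has three primary scores, each at .05, and no rule for combining them. Under an any-score rule the type I error is about 11 to 14%. If staff-report and self-report must both succeed, t-test power is about 0.64 to 0.69; if all three scores must, it is about 0.51 to 0.66.

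The 14.3% (independence) and the 0.801 and 0.656 power figures need no assumption about correlations between scores. The other figures rest on the correlations stated above, and all power figures rest on d = 0.5 for each score tested. The power shortfall applies to the t-test calculation that the article presents; whether the planned model has the same shortfall cannot be decided from the document. Nor does the document favour one SDAS score over the other, or support making the follow-up secondary, since a maintained effect at 12 weeks is part of the stated aim.

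**What to change.** Before results are known, state one success rule for the group x time test of each primary score in Statistical analysis, and make Power and sample size calculation match it. Any one of these would do:

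- **(a) Holm across the three scores.** Restate t-test power as about 0.66 for a given score at the first step.
- **(b) Both sources required.** Name one SDAS score, require it and the AVL each to succeed at .05, and restate power as about 0.64 to 0.69 with the assumed correlation.
- **(c) A fixed order chosen by the sponsor.** Test each score at .05 only if the one before it succeeded, and say that the .80 applies to the first score only.

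If the sponsor wishes to credit the repeated-measures model with higher power, the sample size section should give the assumed pre-post correlation and the contrast to which it applies.

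The cost is a few sentences in two sections. The downside is a less favourable stated power under (a) or (b), or scores tested only conditionally under (c). None of the options requires a larger sample, provided the restated power is accepted.

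### The group x time test compares change from baseline, which is less precise than adjusting for the baseline already collected, and the stated power belongs to a different test

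*Protocol article*

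**What the plan says.** Protocol article, Statistical analysis: the model is a multilevel repeated-measures linear regression. "Differences in scores between pre-intervention, post-intervention and follow-up assessments and between intervention and control group will be examined for the dependent variables", so the pre-intervention score is an outcome and not a covariate. The treatment test is then given: "Effects of VRAPT will be tested with group x time interaction terms". On covariates it says only "Risk factors for aggression will be used as covariates in the linear regression models". These factors are not named, and the outcome's own baseline value is not mentioned as a covariate.

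Protocol article, Power and sample size calculation: "An effect size of 0.5 is considered as moderate". The calculation rests on "an independent two-sided t-test to evaluate the main outcome", from which "64 subjects are required in each condition, total" 128. No correlation, repeated measure or interaction enters it.

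Both primary measures have a value before the intervention. The AVL is taken at T1, T2 and T3. The SDAS is scored weekly for at least 12 weeks before training and, according to Procedure, for 32 weeks in all.

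**The concern.** In a model with group, time and group x time, where the first time point is the baseline, the interaction at a later time is the difference between arms in mean change from baseline. Subtracting the baseline gives it a weight of one, whatever its correlation with the later score. When that correlation is moderate, this adds noise. Regression on the baseline uses the best weight and is more precise with the same data.

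Two things are at stake. The primary comparison may be less precise than the collected data allow. And the power statement describes a test that the analysis section does not plan to use, so it does not show what power the planned test has.

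**Working it through.** **Inputs.** From the article: d = 0.5, two-sided alpha .05, power .80, 64 per arm; 12 SDAS baseline weeks, 12 follow-up weeks, and 32 − 12 − 12 = 8 weeks between. Assumed, because the article gives none: the correlation ρ between baseline and later score, equal variances at both times, and d scaled to the SD of a single score.

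**1. The plan's own figure.** For an independent two-sided t-test at d = 0.5, the noncentral t distribution gives power 0.795 at 63 per arm and 0.801 at 64. The stated 64 per arm reproduces as a t-test on one score per patient.

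**2. Variance of each comparison, relative to that t-test.**
- Later score only: 1
- Change from baseline (the interaction): 2(1−ρ)
- Adjusted for baseline: 1−ρ²
- Change divided by adjusted: 2(1−ρ)/(1−ρ²) = 2/(1+ρ), which is above 1 for every ρ < 1

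**3. Power at 64 per arm**, putting d/√(relative variance) into the same t-test. For example, at ρ = 0.3: 0.5/√1.40 = 0.423 for change and 0.5/√0.91 = 0.524 adjusted.

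| ρ | Relative variance, change | Relative variance, adjusted | Power, change | Power, adjusted | n per arm for .80, change / adjusted |
|---|---|---|---|---|---|
| 0.3 | 1.40 | 0.91 | 0.66 | 0.84 | 89 / 59 |
| 0.4 | 1.20 | 0.84 | 0.73 | 0.87 | 77 / 54 |
| 0.5 | 1.00 | 0.75 | 0.80 | 0.90 | 64 / 49 |
| 0.6 | 0.80 | 0.64 | 0.88 | 0.94 | 52 / 42 |
| 0.7 | 0.60 | 0.51 | 0.95 | 0.98 | 39 / 34 |
| 0.8 | 0.40 | 0.36 | 0.99 | 1.00 | 27 / 24 |

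The change comparison equals the planned t-test where 2(1−ρ) = 1, that is ρ = 0.5. It is weaker below that and stronger above.

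**4. Check in a mixed model.** 120 trials were simulated at ρ = 0.3, with 64 per arm, three time points and a random intercept. With a free group term, the interaction equalled the difference in mean change to rounding error. Its mean standard error was 0.208 (formula: √(2 × 1.40/64) = 0.209). A time-invariant risk factor added as a covariate left it at 0.208, so a covariate of that kind does not recover the precision. Removing the baseline group term brought it to 0.169 (formula for adjustment: √(2 × 0.91/64) = 0.169).

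**5. SDAS period means.** With weekly intraclass correlation c and exchangeable weeks, the variance of a mean over k weeks is c + (1−c)/k, and the covariance between two period means is c. For c = 0.2 and 12 weeks in each period, the variance is 0.2 + 0.8/12 = 0.267 and ρ = 0.2/0.267 = 0.75, so adjusted/change = (1 + 0.75)/2 = 0.875. Over c from 0.2 to 0.7, and 8 or 12 later weeks, ρ runs from 0.71 to 0.97 and adjustment lowers the variance by about 1% to 13%.

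**The case against.** Group x time is a standard and valid test. Sizing on a simple t-test and analysing with a mixed model is common, and it is conservative when ρ exceeds 0.5. The article calls the AVL's test–retest reliability good, without a figure, which leans towards a higher ρ. For the SDAS, averaging over weeks makes ρ high, so the low-ρ rows of the table do not describe it. The free group term is also inferred: if arms were constrained equal at baseline, the interaction would be about as precise as adjustment. All of this stands, and it limits the size of the point. It does not remove it. The article states no such constraint, its wording on differences between the groups points to a free term, and adjustment is at least as precise at every ρ.

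A reader might go further in three ways that the document does not support.
- That the SDAS has no usable contrast, because Table 1 shows no SDAS score at the pre-intervention, post-intervention or follow-up columns. A later sentence of the same section compares the arms across the periods preceding, covering and following training or waiting, and these are the three SDAS periods of Table 1.
- That weekly SDAS scores will inflate the false-positive rate through serial correlation. This needs a random-intercept model with independent residuals fitted to every weekly score. The article specifies neither, and a condensed article commonly leaves the covariance structure to the full plan.
- That the trial is underpowered. This needs ρ below 0.5, which the article neither gives nor excludes. It also does not say to which SD the 0.5 refers.

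**Conclusion.** The point holds as one of efficiency and consistency. On its ordinary reading the planned test is a change-from-baseline comparison, with variance 2/(1+ρ) times that of a baseline-adjusted one: 1.54 times at ρ = 0.3, 1.33 at 0.5 and 1.18 at 0.7. The loss could matter for the AVL, where each time point is one score. It is probably small for SDAS period means. The direction rests only on the free group term; the size rests on assumed correlations and equal variances. No bias is shown.

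The stated .80 is correct for the t-test named, but it is not the power of the planned test, and no shortfall is demonstrated.

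**What to change.** Reword the primary analysis so that the effect tested is the arm difference adjusted for the patient's own baseline:
- **AVL:** T2 and T3 as outcomes, T1 as covariate (with its slope free to differ between T2 and T3), and the arm difference tested at the chosen time or times.
- **SDAS (peak and general):** during-intervention and post-intervention period means as outcomes, with the 12-week baseline mean as covariate.
- **Power:** restate it for this model, with an assumed correlation and the SD to which 0.5 refers.

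Once the baseline has become a covariate, the group x time term must not remain the test. It would then ask only whether the effect differs between the later times.

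Covariate adjustment is the safer form here than constraining baseline means to be equal. According to Procedure and Randomization, allocation precedes the baseline measures and is told to participants and clinical teams, so the arms could already differ by then. The timing of randomisation is a separate matter and need not change for this fix.

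The cost is analysis wording and a short power statement; no data or patients are added. As the trial is ongoing, the change should be dated before outcomes are compared by arm.

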## Discussion

The main goal of this study is to investigate the effectiveness of VRAPT on reactive aggressive behavior of forensic psychiatric inpatients. This study will be the first to evaluate the effectiveness of a VR intervention targeted at reducing reactive aggressive behavior of forensic patients. The hypothesis of the study is that VRAPT will decrease both self-reported and staff-reported aggressive behavior.

Inpatient aggressive behavior is a predictor for future aggression in society, because inpatient aggression is related to non-compliance, higher treatment dropout, and more personality disorders [44]. Current interventions focusing on the reduction of aggressive behavior have several limitations [18]. First, exposure to provocation in highly secured forensic settings is limited. Thus, it is not possible to practice and train forensic patients to control the anger of others and themselves by provoking them in real life social situations. Second, social skill training to prevent aggression by others is limited, and is usually practiced only in treatment groups and role play. Third, engaging forensic patients in treatment is challenging. Attrition is high, as many of them do not like treatment, and/or find it difficult to apply cognitive therapeutic insights. Fourth, it is difficult to evaluate objectively and reliably to what extent patients have learnt to regulate their aggressive impulses, which makes forensic risk assessment complicated.

Addressing the previously listed limitations, VRAPT has several advantages. First, patients can have the opportunity to practice with difficult behavior and additionally gain tools to cope with aggression, instead of leaving the situation or avoiding angry emotions. Second, VR is an interactive tool that allows trainers to provoke and trigger aggression during the training. Often this is described as a difficult aspect by trainers, however, with VRAPT the trainers feel safer in provoking participants, as the participant faces the virtual character and the trainer’s voice is transformed. This also works the other way around: because the trainer ‘plays’ as the virtual character, it is safer for the participant to express his aggression without worrying about the therapeutic relationship. Third, VRAPT is an experiential, behavioral training, focusing on practicing behavior and not necessarily on gaining cognitive therapeutic insights. Fourth, objective and reliable assessment of aggression in real life situations on treatment wards is difficult. Therefore, in the VRAPT real-time measurements of physiological arousal are included. These measurements help to gain more insight into arousal of the patients. Moreover, not only self-report measurements, but also staff observations are recorded. All these aspects are of specific importance because forensic psychiatric patients are at an increased risk of behaving in an aggressive manner.

From a broader perspective, this study will shed light on the effectiveness of VR interventions in forensic populations. If proven to be effective, VRAPT could be a useful addition to current interventions in forensic psychiatry and be implemented in other forensic psychiatric centers, especially as evidence based interventions to reduce aggressive behavior are scarce [14]. In addition, reducing aggression of forensic patients is of great importance for patients, but also for staff working in forensic psychiatric centers, as many fellow patients and treatment staff are victimized by aggression of forensic patients. Because patients can practice safely with difficult situations that they can expect to be confronted with in the outside world, VRAPT may be an important contribution to the preparation for reintegration into society. Thus VRAPT is expected to lead to improvement of psychological, social and emotional well-being of patients and treatment staff.

### Trial status

Ongoing.

## Abbreviations

AVL: Aggression Questionnaire
BDHI-D: Buss-Durkee Hostility Inventory-Dutch
BIS-11: Barratt Impulsiveness Scale
CTQ-SF: Childhood Trauma Questionnaire – Short Form
DSM: Diagnostic and Statistical Manual of Mental Disorders
FPCs: Forensic Psychiatric Centers
GAM: General Aggression Model
GSR: galvanic skin response
HIBT: Hostile Interpretation Bias Task
HR: heart rate
IPQ: Igroup Presence Questionnaire
IQ: Intelligence quotient
NAS-PI: Novaco Anger Scale – Provocation Inventory
NTR: Dutch Trial Register
NWO: Netherlands Organization for Scientific Research
PTSD: Post-Traumatic Stress Disorder
RCT: Randomized Controlled Trial
RPQ: Reactive-Proactive Questionnaire
SDAS: Social Dysfunction and Aggression Scale
SIP model: Social Information Processing model
STAXI-2: State-Trait Anger Expression Inventory-2
TAU: Treatment As Usual
TBS-order in Dutch: ter-beschikking-stelling: this translates as ‘detained under hospital order’
VR: Virtual Reality
VRAPT: Virtual Reality Aggression Prevention Training
